## **List of Abbreviations**

AE- Adverse Events

AIDS- Acquired Immunodeficiency Syndrome

AMI- Acute Myocardial Infarction

ART- Anti- retroviral treatment/ therapy

ARV- Anti- retroviral

ASA- Acetyl Salicylic Acid

BMI- Body Mass Index

COX- Cyclo- oxygenase

CPL- Central Pathology Laboratory

CRFs- Case Report Forms

CTCs- Care and Treatment Centres

DSMB- Data and Safety Monitoring Board

FBP- Full Blood Picture

GCLP- Good Clinical and Laboratory Practice

GCP- Good Clinical Practice

HAART- Highly Active Antiretroviral Therapy

hCG- human Chorionic Gonadotrophin

HIV- Human Immunodeficiency Virus

ICH- International Council for Harmonization of Technical Requirements for Pharmaceuticals for Human Use

JSI- John Snow, Inc.

LFT- Liver Function Test

MCRL- MUHAS Clinical Research laboratory

MDH- Management and Development for Health

MNH- Muhimbili National Hospital

MoHCDGEC- Ministry of Health, Community Development, Gender, Elderly and Children

MPAs- Monocyte- Platelet Aggregates

MUHAS- Muhimbili University of Health and Allied Sciences

NIMR- National Institute for Medical Research

NSAIDs- Non-Steroidal Anti- Inflammatory Drugs

PAI- PharmAccess International

PASADA- Pastoral Activities and Services for People with AIDS Dar es Salaam Archdiocese

PBMCs- Peripheral Blood Mononuclear Cells

PI- Principal Investigator

PLHA- People Living with HIV and AIDS

PSGL- 1- P- Selectin Glycoprotein Ligand 1

RFT- Renal Function Test

SAEs- Serious Adverse Events

sCD14- Soluble CD14

SOPs- Standard Operating Procedures

sP- selectin- Soluble P- selectin

SUSAR- Suspected Unexpected Serious Adverse Reaction

TFDA- Tanzania Food and Drug Authority

TNF-  $\alpha$ - Tumour Necrosis Factor- alpha

UNAIDS- Joint United Nations Programme on HIV/ AIDS

WHO- World Health Organization

**Definitions.**

1. **Adherence to ART** will be defined as greater than 90% adherence by pill count.
2. **Adverse Event (AE)** will be defined as any untoward medical occurrence in a patient enrolled into this study regardless of its causal relationship to study treatment.
3. **Serious Adverse Event (SAE)** will be defined as any AE that results in death; or is immediately life threatening; or requires inpatient hospitalization; or requires prolongation of existing hospitalization; or results in persistent or significant disability/incapacity; or is a congenital anomaly/birth defect.
4. **Non-Serious Adverse Event** will be defined as any AE that does not result in death; or is not immediately life threatening; or does not require inpatient hospitalization; or does not require prolongation of existing hospitalization; or does not result in persistent or significant disability/incapacity; or is not a congenital anomaly/birth defect.
5. **Suspected Unexpected Serious Adverse Reaction (SUSAR)** will be defined as any SAE that is both suspected to be related to the study treatment and is unexpected (i.e. not consistent with applicable product information).
6. **Morbidity** will be defined as number of health facility/ hospital visits for medical attention/ care because of illness and/or number of health facility/ hospital admissions.
7. **All- cause mortality** will be defined as confirmed death of any cause with certification of death by medical practitioner or a verbal or telephone confirmation of death from a relative or friend.
8. **Clinical conditions associated with death** will be defined as those clinical conditions diagnosed within one month prior to or at time of death or were thought to be related to death after review of the medical records.
9. **Low- dose- aspirin (ASA)** will be defined as ASA dosages between 75mg and 325mg taken every day.
10. **Compliance to ASA** will be defined as adherence to ASA therapy for at least 22 days in a month.

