### **1.6.3 Secondary objectives**

The secondary objectives of the proposed study are:

1. To compare the CD4 counts measured at 3 and 6 months among HIV- infected individuals after initiating ARV therapy alone or ARV therapy and 75mg ASA.
2. To compare the plasma levels of immune activation biomarker (sCD14) measured at 3 and 6 months among HIV- infected individuals after initiating ARV therapy alone or ARV therapy and 75mg ASA.
3. To compare the plasma levels of platelet activation biomarker (P- selectin) measured at 3 and 6 months among HIV- infected individuals after initiating ARV therapy alone or ARV therapy and 75mg ASA.
4. To compare percentage of activated T cells (CD38 positive and HLA-DR positive T cells) measured at 3 and 6 months among HIV- infected individuals after initiating ARV therapy alone or ARV therapy and 75mg ASA.
5. To compare percentages of exhausted T cells (PD1 positive T cells) measured at 3 and 6 months among HIV- infected individuals after initiating ARV therapy alone or ARV therapy and 75mg ASA.
6. To compare morbidity among HIV- infected individuals initiating ARV therapy alone or ARV therapy and 75mg ASA.
7. To compare all-cause-mortality among HIV- infected individuals initiating ARV therapy alone or ARV therapy and 75mg ASA.
8. To determine level of adherence to ARV therapy among HIV- infected individuals initiating ARV therapy and ASA or placebo.

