## **2.7 Primary and Secondary Outcome Measures**

The primary outcome of interest will be virological response. The main virological outcome that will be observed will be the proportion of patients in different arms reaching viral loads of < 50 copies/ millilitre at months 2, 3 and 6 (indicating viral suppression) and > 1000 copies/ millilitre at month 6 (indicating virologic failure).

The secondary outcomes will be immunologic response measured by CD4 count and clinical responses measured by morbidity and death from any cause. With the use of ART alone there is an increment of 30% at 3 months in CD4 count from baseline value(56). With the addition of ASA to the ART, it is expected that the CD4 count will rise by > 30% from baseline value at months 3. Other secondary outcome measures will be plasma levels of sCD14 and sP- selectin, percentage

of activated T cells (CD38 positive and HLA-DR positive T cells), percentage of exhausted T-cells (PD-1 positive T cells), percentage adherence to ART and compliance to study medications, adverse events. The levels of sCD14 and sP- selection are expected to drop to those of non- HIV infected population by 6 months(16).

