#### **2.11.7 Other assessments**

During clinical evaluation at each monthly visit, the attending clinician will look for occurrence of any AE since the last visit and all the AEs will be recorded in a specially designed form.

Assessment of compliance to study drugs will be by pill count. Patients' remaining monthly tablets of their study drugs will be counted to ascertain compliance at each monthly follow up visit. Overall compliance will be the average of the monthly compliances.

Adherence to ART will be measured based on pill counts. Patients' will be asked to return with the ARV drug bottles every time they come to the clinic for their follow up visits. At each visit, pills remaining in bottles will be counted by the study doctor and the percentage of these pills to the dispensed pills during the previous visit will be calculated based on the dose and the number of days dispensed. The pill count adherence percent will be obtained by dividing the number of pills consumed by the total number of pills dispensed at the last visit and multiplied by 100. Overall adherence will be the average of the monthly adherences. For patients who will not last in the study for all the 6 months, their adherence to ART will be calculated by taking the average of the monthly adherences of months they have been in the study. Greater than 90% overall adherence by pill count will be considered adherence(58).

Morbidity will be defined as health care facility visits for medical attention/ care because of illness and/or the number of admissions to a health care facility/ hospital. At each monthly visit, patients will be asked if they visited any health care facility to seek medical care/ treatment and/ or if they were admitted on medical basis since last visit. The reason for visit or admission will be traced from the patient or medical and/or clinical records respectively.

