### **2.13.2 Population to be analyzed**

The subject population whose data will be subjected to the study to analyses is the intention to treat population.

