### **2.13.3 Statistical Analysis Plan**

The data will be double entered into a computer by two different data entry clerks and the entered data will then be verified and cleaned before being subjected to analysis using the SPSS statistical program. Intention to treat analysis will be done.

Chi- square or Fisher's exact test will be used for comparison of proportions and Student's t test for comparison of means between the two treatment groups.

Descriptive statistics will also be used where appropriate. A two tailed P-value of  $<0.05$  will be considered significant.

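### Morbidity is an unscaled count of illness visits and/or admissions, and no listed test uses time at risk, so unequal death or loss between arms would distort the comparison

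*Protocol*

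**What the plan says.** Secondary objective 6 in Protocol 1.6.3 is "To compare morbidity among HIV- infected individuals initiating ARV therapy alone or ARV therapy and 75mg ASA", and 2.7 lists among the secondary outcomes "clinical responses measured by morbidity and death from any cause". Item 6 of the Definitions says that morbidity "will be defined as number of health facility/ hospital visits for medical attention/ care because of illness and/or number of health facility/ hospital admissions", and 2.11.7 repeats this with small changes. Neither place gives a rate, a person-time denominator, or a rule for death or incomplete follow-up.

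On data collection, 2.11.7 states: "At each monthly visit, patients will be asked if they visited any health care facility to seek medical care/ treatment". The same question covers admissions since the previous visit. Section H of the follow-up CRF (Appendix 3) records start and stop dates for each morbidity period.

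On analysis, 2.13.2 states: "The subject population whose data will be subjected to the study to analyses is the intention to treat population". Section 2.13.3 names chi-square or Fisher's exact test for proportions and "Student's t test for comparison of means between the two treatment groups". The Abstract gives the same three tests for the study outcomes, with descriptive statistics where suitable.

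For another outcome, 2.11.7 does allow for short follow-up: "For patients who will not last in the study for all the 6 months, their adherence to ART will be calculated" as the mean over the months in which they took part. Morbidity has no such rule.

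**The concern.** A count of illness visits depends on how often a patient falls ill and on how long the patient is observed. The protocol fixes the count and lists only tests that ignore the second part. Someone seen for three of the six months has half the expected count of someone with the same illness rate who is seen throughout.

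Mortality is itself compared between arms (secondary objective 7), so equal observation time cannot be taken for granted. If one arm has more deaths or losses, its morbidity will look lower for that reason alone. If those who leave are also sicker, a true excess in that arm can be hidden.

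**Working it through.** **The plan's own figure.** The protocol gives no figure for morbidity. Its 227 per arm (2.13.1) is for viral load at week 8. For 75% v 86%, two-sided 0.05, 80% power and no continuity correction, n = 203, and 203/0.90 = 225.6, so 226. That agrees with 227 to within one patient but says nothing about morbidity.

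**Inputs from the protocol.** Six months of monthly follow-up (Abstract, 2.10) and 10% loss (2.13.1).

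**Assumptions.**
- Leaving times are uniform over six months.
- Leavers have R times the illness rate of the others, with R = 1, 2 or 3.
- An unequal split is 15% v 5%, which still averages 10%.
- The question is asked at monthly visits, so only completed months are counted. Leavers then contribute on average m = (0+1+2+3+4+5)/6 = 2.5 months. If part-months were also captured, m = 3.

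**Step 1: level within one arm.** With a fraction p leaving,

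observed/true = [(1 − p)·6 + p·R·m] / [(1 − p)·6 + p·R·6].

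For p = 0.10 and m = 2.5:
- R = 1: (5.4 + 0.25)/6 = 5.65/6 = 0.942, or 5.8% low.
- R = 2: (5.4 + 0.5)/(5.4 + 1.2) = 5.9/6.6 = 0.894, or 10.6% low.
- R = 3: (5.4 + 0.75)/(5.4 + 1.8) = 6.15/7.2 = 0.854, or 14.6% low.

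With m = 3 and R = 1 the shortfall is 5.0%. If leavers are seen for anything from 25% to 75% of follow-up, it runs from 0.10 × 0.75 = 7.5% down to 0.10 × 0.25 = 2.5%.

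When p, m and R are the same in both arms, the factor is common to both and cancels in the ratio.

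**Step 2: ratio between arms, 15% v 5% leaving.**
- R = 1, m = 2.5: (5.1 + 0.375)/(5.7 + 0.125) = 5.475/5.825 = 0.940. The true ratio is 1.000.
- R = 1, m = 3: 5.55/5.85 = 0.949. The true ratio is 1.000.
- R = 2, m = 2.5: (5.1 + 0.75)/(5.7 + 0.25) = 5.85/5.95 = 0.983. The true ratio is 6.9/6.3 = 1.095.
- R = 2, m = 3: 6.0/6.0 = 1.000. The true ratio is again 1.095.

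**Step 3: error rate of a t test on the raw count.** This was simulated with 227 per arm, gamma-Poisson counts (shape 1), part-months captured, R = 1, no treatment effect and 4000 runs, at 1 and 3 events per six months. The Monte Carlo standard error near 5% is √(0.05 × 0.95/4000) = 0.3 percentage points.
- 10% v 10% leaving: 5.2% and 5.0%.
- 15% v 5% leaving: 6.6% and 8.0%.
- 30% v 10% leaving: 12.4% and 16.7%.

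**Step 4: what a person-time analysis recovers (m = 2.5, 15% v 5%).**
- R = 1: 5.475/5.475 v 5.825/5.825, ratio 1.00. The bias is removed.
- R = 2: 5.85/5.475 = 1.068 v 5.95/5.825 = 1.021, ratio 1.046 against 1.095. About half the excess is recovered.
- One leaver in six goes before the first monthly visit and has no observed months. At 10% loss that is 227 × 0.10/6 = 3.8 patients per arm, whom an offset model cannot include.

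**The case against.** The strongest reply is that much of this is silence, of a kind often left to a separate SAP, and that the planned figures show no bias between arms. Several stronger readings are tempting, and the documents do not support them.

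- **That the protocol assigns the t test to morbidity.** It does not. The t test is the listed test that fits a count, but a chi-square test on the proportion with any visit is also open. That choice has the same exposure problem.
- **That an early death is scored 0, the best value.** No scoring rule is stated. Such a patient could equally be treated as missing, and a patient who dies later may have had several visits or admissions first.
- **That everyone who stops early is cut short.** Patients withdrawn from treatment are followed to six months (2.9.6.1) and keep their scheduled visits where feasible (2.9.6.2). Observation is cut short only by death, loss to follow-up or refused visits.
- **That nothing after the last visit can be known.** Absent patients and next of kin are telephoned (2.9.6.2), records are reviewed after a death (2.11.7), and inpatient admissions are reportable as SAEs (2.12). The protocol does not say that any of these feeds the morbidity count.
- **That an excess would be reversed.** The value 0.983 depends on counting whole months only. With part-months the ratio is 1.000, so the excess is masked.

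The point about silence stands only in part. The protocol has its own section headed as a statistical analysis plan, and with the Abstract it limits comparisons of outcomes to three tests that take no account of time at risk. It also adjusts adherence for months in the study and collects the dates that morbidity would need.

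**Conclusion.** The point holds in limited form. The outcome is an unscaled count, the listed tests ignore time at risk, and the dates that would supply it have no stated use.

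At the planned 10% loss, balanced in number, timing and relative illness of leavers, both arm means are about 6% low, the comparison is unbiased and the t test keeps its size. A reader might infer that the planned loss by itself biases the result; it does not. Bias needs unequal death or loss. At an assumed 15% v 5%, the ratio is about 0.94 (0.95 with part-months) when the truth is 1.00. If leavers are twice as ill, a true ratio of 1.095 appears as 0.98 to 1.00.

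These sizes rest on the assumed split, uniform leaving times and assumed rate ratios. The true ratio also credits leavers with events up to month 6, which is meaningful for those lost but not for those who died. Severity is minor to moderate, because this is a secondary outcome.

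**What to change.** - **Definitions item 6 and 2.11.7:** define illness visits and admissions as two separate counts, each per person-month observed, with observed time taken from the period dates in CRF section H. This also resolves the and/or wording.
- **2.13.3:** compare arms by negative binomial or overdispersed Poisson regression, with log observed months as offset and site as covariate, since randomisation is done separately at each site (2.9.3). Report the rate ratio with its 95% CI, beside deaths and the number of patients with no observed time in each arm.

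The cost is a change of wording, and no new data are needed. There are three downsides: a model replaces a simple test, patients with no observed time drop out of it, and the offset reduces but does not remove bias from informative loss (1.046 against 1.095 in the example).

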## **ABSTRACT**

**Background;** Despite the introduction of antiretroviral (ARV) therapy, HIV is still a public health problem in Eastern and Southern Africa. The wide spread use of the ARV drugs has improved the life expectancy of people living with HIV and/ or acquired immunodeficiency syndrome (AIDS). As a result, there has been an increase in the prevalence of and mortality from non- AIDS complications such as non- AIDS defining cancers, liver, pulmonary and cardiovascular diseases. The increase in the non – AIDS complications especially the cardiovascular disease risk is linked to platelet and immune activation. Antiretroviral therapy (ART) does not completely abolish the immune activation and the platelet activation making it a necessity to find additional therapy to the conventional ART therapy that will decrease the occurrence of these non- AIDS complications and their associated morbidities. Aspirin or acetyl salicylic acid (ASA) has shown promise as such an additional drug. In addition, ASA appears to have an array of beneficial effects in the HIV infected individuals. ASA is reported to cause a reduction and maintenance in HIV load, significantly increase CD4 counts and halt the clinical HIV disease progression. Literature shows that additional therapy to ARV drugs may compromise adherence to ART among HIV- infected individuals. However, when addition of a pill is associated with significant benefit, the addition of a pill or pills may be justifiable. For example, addition of medication for opportunistic infection, methadone maintenance therapy and antidepressants has been reported to improve adherence to ART among HIV- infected patients in some studies. Therefore, considering the reported benefits of ASA in the HIV- infected population, it is important to study the effect of the addition of ASA on both the HIV disease progression and the adherence to ARV drugs.

**Objective(s):** To determine the effect of low dose of ASA on HIV disease progression and adherence to anti- retroviral therapy among HIV-infected individuals initiating ARV therapy.

**Materials and Methods:** The study will be a phase IIA randomized double blind, placebo-controlled trial with two study groups involving 454 antiretroviral drugs naïve adult patients initiating ART who are attending HIV clinics at **Mwananyamala** and Mbagala Rangi Tatu in Dar es Salaam. Patients in the two study groups will be receiving, in addition to ARV drugs, 75 mg ASA or placebo once daily for six months. They will be followed up monthly for a period of six months. Blood samples will be collected at baseline for all the tests and at months 6 for lipid profile, full blood picture (FBP), renal function test (RFT) and liver function test (LFT), at

months 3 and 6 for CD4 count, at months 2, 3 and 6 for HIV viral load and at months 3 and 6 for plasma levels of soluble CD14 (sCD14), soluble P- selectin (sP- selectin) and for markers of T cell activation and exhaustion. Urine will be collected to exclude pregnant women. The primary outcome will be virological response i.e. the proportion of patients in the two arms reaching viral loads of < 50 copies/ millilitre at months 2, 3 and 6 (indicating viral suppression) and > 1000 copies/ millilitre at month 6 (indicating virologic failure). The secondary outcomes will be immunologic response measured by CD4 count and clinical responses measured by morbidity and death from any cause. Other secondary outcome measures will be plasma levels of sCD14 and sP- selectin, percentage of activated T cells (CD38 positive and HLA-DR positive T cells), percentage of exhausted T-cells (PD-1 positive T cells), percentage adherence to ART and compliance to study medications, adverse events. Data will be analysed by intention to treat. The study outcomes in the two treatment groups will be compared using Chi- square, Fisher's exact or student's t tests and descriptive statistics will be used where appropriate.

**Budget of the study;** The estimated budget for the proposed study 123,722,026.40 Tshs

# **1. INTRODUCTION**

## **1.1 Background**

HIV infection continues to be a global public health problem. According to the Joint United Nations Programme on HIV/ AIDS (UNAIDS) data of 2017, approximately 36.7 million people were living with HIV worldwide with the Eastern and Southern Africa being a highly-burdened region contributing more than half of the cases in 2016. Additionally, the Eastern and Southern Africa had the highest percentage of the new HIV infections compared to the other regions in the world(1) leading to more burden of HIV infection in the future. Although there has been a global decline in AIDS- related deaths from 2004 to recent years and that the Eastern and Southern Africa had the sharpest decline, deaths from HIV/ AIDS are still high in this part of the world(1).

In Tanzania, by 2016, a total of 1.4 million people were living with HIV and AIDS- related deaths were 31000 which is a 50% decline from about five years previously. However, this number is still high(1). The decrease in AIDS- related mortality, in Tanzania and elsewhere, is mostly a result of the introduction and widespread use of the highly active antiretroviral therapy (HAART)(2).

Since the introduction of ART and the highly active antiretroviral therapy, people living with HIV and AIDS (PLHA) are now living longer than before (have improved life expectancy)(2,3). The improved life expectancy is a result of stable or improved CD4 counts, suppressed HIV loads and clinical benefits provided by the ART(2). Despite the improved life expectancy, when compared to the general population, PLHA still die earlier(3). This may be because, PLHA are living longer to experience age-related co- morbidities and that there has been an increase in the prevalence of and mortality from non-HIV/AIDS complications such as non- AIDS defining malignancies, hepatic, pulmonary and cardiovascular diseases among them(2).

Cardiovascular disease has become of great importance as a cause of morbidity and mortality among the HIV- infected patients(4–6). Particularly, cardiovascular disease is now one of the top causes of deaths in the HIV- infected population (7,8). The risk of cardiovascular diseases such as myocardial infarction (MI) and sudden cardiac death in both the treated and untreated HIV- infected individuals is significantly higher than in the HIV- non- infected ones. Among the HIV- infected population, the risk is higher for those on antiretroviral treatment compared to those who are treatment naïve(9) suggesting that the metabolic adverse effects of the ARV drugs may have a role. Indeed, the incidence of cardiovascular disease is reported to be higher in the ART-

successfully treated HIV- infected patients than the HIV non- infected ones(10). However, the mechanism of the increased cardiovascular disease risk among HIV- infected is still not completely understood. Studies have reported an interplay of many other factors apart from the metabolic adverse effects of the ARV drugs. Some of such factors are the high prevalence of traditional risk factors for cardiovascular disease (smoking, hypertension, diabetes and dyslipidaemia)(11) within the HIV- infected individuals, the replication of HIV itself and a low CD4 count (12,13). Prolongation of life is also a postulated factor as people live longer enough to develop cardiovascular diseases. Additionally, chronic immune activation is partially attributed to the increased risk for cardiovascular disease in PLHA. Immune activation (of both the innate and adaptive immune response) is reportedly higher in the HIV infected population than the HIV- non infected population and is said to result from low level viral replication, adipose tissue dysfunction, coinfection and translocation of microbial products from a damaged gut.

Among activation of other cells of the immune system, less clearly, T cell activation has been reported to play a role in the development of cardiovascular disease in the HIV- infected individuals. The levels of T cell activation and T cell exhaustion are defined by the expression of cellular markers CD38, HLA- DR and PD-1, respectively. HIV- infected individuals exhibit increased markers of T cell activation and studies have shown that the ARV naïve HIV- infected individuals have higher frequencies of activated T cells than those on ART with viral suppression. Furthermore, it is reported that even with successful treatment with ART, percentages of activated T cells remain higher than in the HIV uninfected population(14–16). Therefore, T cell activation may be one of the factors that can be linked to increase risk for cardiovascular disease in HIV- infected individuals. Indeed, it has been shown that T cell activation is associated with subclinical atherosclerosis among PLHA(17).

Apart from T cell activation, monocyte activation also is associated with vascular disease in the HIV- infected patients(18–20). Monocytes are persistently activated in HIV- infected patients. Activated monocytes are associated with HIV pathogenesis and progression and development of cardiovascular disease. Following activation, monocytes produce, among other molecules, sCD14 by enzymatic shedding of CD14 from the plasma membrane. The liver also secretes sCD14 as an acute- phase protein in response to interleukin- 6. In the HIV- non- infected elderly individuals and those with chronic kidney disease, sCD14 has been linked to cardiovascular diseases such as

MI(21,22). Likewise, in the HIV- infected sCD14 is reportedly associated with cardiovascular disease(23). Plasma levels of sCD14 are higher in the HIV- infected patients as compared to those in the general population(16,24). Different studies have reported that sCD14 levels do not return to normal values even in the ART- virologically suppressed patients(24–27). Elevated levels of sCD14 in the PLHA may reflect the extent of monocyte activation (as part of the chronic immune activation) among these individuals. All these data therefore, suggest that monocyte activation (as a component of immune activation) together with the associated biomarker (sCD14) may play a role in the pathogenesis of HIV- related cardiovascular disease.

Different causes for monocyte activation in the HIV- infection have been put forward and activated platelets is one of them. There is increased platelet activation in the HIV- infected individuals(28) and activated platelets express, among other molecules, P- selectin to which monocytes bind via P-selectin glycoprotein ligand-1 (PSGL-1) to form monocyte- platelet aggregates (MPAs). P-selectin is one of the several adhesion molecules expressed by platelets whose major function is to facilitate the process of clot or thrombi formation. In the platelets, P- selectin is stored in the alpha granules and when platelets are activated, P- selectin quickly moves to the cell surface of the platelets (P- selectin expression). The expression of P- selectin is short lived and the molecule is degraded or recycled following its quick internalization in the cell. P- selectin can be secreted into the circulation in a soluble form giving the sP- selectin. It is reported that elevated levels of sP-selectin are associated with atherosclerosis and thrombosis and are predictive of future adverse cardiovascular events such as MI and stroke(29–31).

It has been shown that in the HIV- infected individuals' plasma levels of sP- selectin are higher than in the HIV non- infected population (27) (secondary to the increased platelet activation)and that the cardiovascular disease risk is increased compared to the non-HIV- infected. There is inconsistency in data with regards to the effect of ART to platelet activation (the levels of sP-selectin). In some reports, sP- selectin levels normalize to non- HIV-infected levels with ART(27) while in some reports the levels do not decrease(32).

Therefore, residual platelet activation and immune activation (as reflected by persistent levels or expression of the respective biomarkers with ART) may be a major shortcoming of the ART, as platelet activation and immune activation are implicated in the increased cardiovascular in PLHA. Decreased platelet and immune activation together with their associated biomarkers may mean

decreased cardiovascular disease risk, reduced HIV disease progression, decreased morbidity and mortality among the HIV- infected population. The use of ARV drugs alone too, results into reduced HIV disease progression, decreased morbidity and mortality through increasing CD4 counts, decreasing both HIV loads and the incidence of opportunistic infections. However, the ARV drugs only partially reduce platelet and immune activation leaving elements of platelet and immune activation which may be associated with cardiovascular disease risk in PLHA. Due to this possible drawback of ARV drugs on immune activation and platelet activation, an additional drug is necessary for effective management of the non- infectious co morbidities in HIV infection.

Aspirin or acetyl salicylic acid (ASA) is a drug with antiplatelet and anti-inflammatory properties. The acute role of ASA on the increased platelet and immune activation in the HIV- infected population has been explored with conflicting findings. In one study, low- dose ASA appeared to lessen both platelet and immune activation and the associated biomarkers in the HIV- infected population in one study(16) while in another study it did not affect biomarkers of immune activation(33). Data on the long-term use of ASA and its effect on platelet and immune activation and consequently, on morbidity and mortality among HIV-infected population are deficient.

ASA was first synthesized in 1897 by chance as a chemist was trying to find an alternative remedy for his father's rheumatism. ASA is one of the long-time known drugs that has been widely used and studied. It belongs to the class of the non- steroidal anti- inflammatory drugs (NSAIDs) and it has a wide range of therapeutic effects depending on the dose given(34).

At low doses, ASA brings about its antiplatelet effects making it a suitable drug for primary and secondary prevention of cardiovascular disease. For anti-inflammatory and analgesic effects, higher doses of ASA are required(34). All these effects of ASA are said to be mediated through inhibition of both isoforms of the cyclo-oxygenase (COX) enzyme affecting the synthesis of prostaglandins, prostacyclins and thromboxanes.

Interestingly, by not so well-established mechanisms ASA appears to have an array of beneficial effects in the HIV infected individuals. ASA is reported to halt the clinical HIV disease progression (35). ASA has been shown to significantly increase CD4 counts, an effect appreciable in a few months to a year of ASA use at moderate to high doses in the HAART naïve patients(36). ASA has also been observed to cause a reduction and a maintenance in HIV load(35,37).

The use of ASA in the HIV- infected individuals is associated with other effects like decrease in p24 antigen, decrease in tumor necrosis factor alpha (TNF- $\alpha$ ), improvement in body weight (together with Body Mass Index [BMI]) and hemoglobin levels(35,36). These effects of ASA in one way or another may contribute to improvement in quality of life, meaning decreased morbidity and/or mortality associated with HIV/ AIDS.

Despite these useful effects, there are risks associated with the use of ASA such as gastrointestinal bleeding and rarely cerebral bleeding which are reported non- fatal or life-unthreatening. It is reported however that these adverse effects are more likely associated with high doses than with low doses and that duration of ASA use does not appear to increase the risk for the adverse effects(38). Thus, the use of ASA at low dose may still be advantageous in the HIV- infected population considering the above-mentioned beneficial effects. Therefore, there is still a need to explore the long- term effects of ASA on morbidity, mortality and the HIV disease progression in general among PLHA.

As it goes with any medications, to achieve successful treatment outcomes medication adherence is very essential. In the management of HIV and AIDS, adherence to ART is crucial for therapeutic outcome since it is a major predictor of virologic suppression, immunologic recovery, disease progression , resistance to ARV drugs, disease progression and death(39–44).

Adherence to ARV medications can be evaluated by various methods such as self-reports using validated questionnaires, patient diaries, pharmacy records, plasma levels, pill counts, electronic monitors and others. For adherence to ART, there is no gold standard method as each method has its merits and shortcomings. Measuring adherence to ART by pill count has been employed in many investigations. Although adherence by pill counts overestimates adherence, it correlates with adherence by electronic monitors ,which is an objective way to measure adherence, and viral load measurements(44–46). In one study, pill count adherence was not significantly different from adherence by self- reports, plasma levels and electronic monitors(44).

Adherence to ARV drugs may be affected by a number of factors including adverse drug effects/ reactions due to drug- drug interactions and high pill burden. There are no reported clinically significant drug-drug interactions between ASA and any of the drugs in ART(47) and hence there are no anticipated adverse drug reactions to compromise adherence when ASA is given together with the ARV drugs. High pill burden of the ARV regimen or from co- medication is one of the

many factors that are associated with non- adherence or low adherence(48,49). Adding ASA, which is not co- formulated with the ARV drugs, to the conventional ARV therapy and other prophylactic drugs for opportunistic infections which are normally given in the management of HIV/ AIDS may increase pill burden among the HIV-infected individuals, consequently affecting their adherence to ARV therapy, which is the backbone of their therapeutic management. Therefore, the proposed study will look at the level of adherence to ARV drugs among HIV- infected individuals taking their ARV drugs and their routine prophylactic drugs against opportunistic infections and the added ASA or placebo.

